## Abstract

**Background:**

Chronic rotator cuff pathology (CRCP) is a common shoulder condition causing pain and disability. Physiotherapy is often the first line of management for CRCP yet there is little conclusive evidence to support or refute its effectiveness and no formal evaluation of its cost-effectiveness.

**Methods/Design:**

This randomised, double-blind, placebo-controlled trial will involve 200 participants with CRCP recruited from medical practices, outpatient departments and the community via print and radio media. Participants will be randomly allocated to a physiotherapy or placebo group using concealed allocation stratified by treating physiotherapist. Both groups will receive 10 sessions of individual standardised treatment over 10 weeks from one of 10 project physiotherapists. For the following 12 weeks, the physiotherapy group will continue a home exercise program and the placebo group will receive no treatment. The physiotherapy program will comprise shoulder joint and spinal mobilisation, soft tissue massage, postural taping, and home exercises for scapular control, posture and rotator cuff strengthening. The placebo group will receive inactive ultrasound and gentle application of an inert gel over the shoulder region. Blinded assessment will be conducted at baseline and at 10 weeks and 22 weeks after randomisation. The primary outcome measures are self reported questionnaires including the shoulder pain and disability index (SPADI), average pain on an 11-point numeric rating scale and participant perceived global rating of change. Secondary measures include Medical Outcomes Study 36-item short form (SF-36), Assessment of Quality of Life index, numeric rating scales for shoulder pain and stiffness, participant perceived rating of change for pain, strength and stiffness, and manual muscle testing for shoulder strength using a handheld dynamometer. To evaluate cost-effectiveness, participants will record the use of all health-related treatments in a log-book returned to the assessor monthly. To test the effect of the intervention using an intention-to-treat analysis, linear regression modelling will be applied adjusting for baseline outcome values and other demographic characteristics. Participant measures of perceived change will be compared between groups by calculating the relative risks and their 95% confidence intervals at each time point using log binomial regression.

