#### Placebo group

As for many procedural interventions, it is difficult to design a placebo treatment that fully mimics a physiotherapy program. However, our aim is to control for the effect of regular contact with a therapist, the belief that treatment will assist CRCP and the therapeutic environment. Participants in the placebo group will receive the same number and length of visits as those in the physiotherapy group but will receive only sham ultrasound and light application of a non-therapeutic gel. Participants in the placebo group will receive no instruction in exercise techniques and no manual therapy. We have used an identical placebo protocol in completed clinical trials of physiotherapy for patellofemoral pain syndrome [36], knee osteoarthritis [37] and shoulder adhesive capsulitis [38]. In these trials, between 68% to 83% of participants in the placebo group thought they had received 'real' physiotherapy or were unsure. Blinding index was 0.49 (bootstrap 95% CI 0.40 to 0.56), interpreted as moderate success of blinding in one study [38]. The placebo participants will not receive any intervention or complete any home exercises during the 12 week follow-up period.

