### Outcome assessment

Demographic information will be collected including age, sex, duration of symptoms, previous investigations and treatment, history of medical conditions, and medication use. Expectation of a beneficial treatment effect will be scored on an ordinal scale from 1 to 5 with higher scores indicating higher expectations.

A number of outcome measures will be collected for this study (Table 3). A combined shoulder pain and disability index (SPADI) will be used to measure changes in shoulder pain and function at final and follow-up time points. This is a self-administered, shoulder-specific index consisting of 13 items divided into two subscales: pain (five items) and disability (eight items) [39]. Responses to each item are recorded on a 11 point Likert scale where 0 = "no pain" or "no difficulty" and 10 = "worst imaginable pain" or "so difficult it required help" for the pain and disability items respectively. The SPADI score is calculated by summing then averaging the two subscales to give a score out of 100 (higher score more pain/disability). It has acceptable test-retest reliability, construct validity and responsiveness [39-41]. We have confirmed the clinimetric properties of this index and found it to be more responsive than other shoulder-specific questionnaires (effect sizes 1.01–1.69) ([name] et al unpublished data).

**Table 3 T3:** Outcome measures

**Primary Outcomes**	**Measurement**
Shoulder pain and disability index (SPADI)	13 items scored on an 11 point Likert scale
Average pain over past week	11 point horizontal numeric rating scale (end descriptors of 0 = no pain and 10 = worst pain possible)
Participant perceived global rating of change overall	Ordinal scale (1-much worse, 2-slightly worse, 3-no change, 4-slightly better, 5-much better)

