### Sample size

Sample size was calculated based upon the ability to detect a 10-point difference in improvement in SPADI score, previously reported to indicate a clinically important improvement (or worsening) of shoulder function [41]. Applying power calculations appropriate for analysis of covariance (adjusting for baseline SPADI score), to detect a difference in 10 week SPADI of 10 units assuming a common between-participant standard deviation of 27 and a baseline to 10 week correlation in SPADI scores of 0.45 (from our pilot study), 91 participants per group will be required to achieve 80% power at a two-sided 5% significance level. Including the 10 week and further 22 week follow-ups in a repeated measures analysis increases the power to 85% assuming a conservative correlation of 0.8 between all post-baseline measurements and a uniform physiotherapy effect. We will allow for a 10% loss to follow-up and aim to recruit 100 participants per group.

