### Data analysis

All analyses will be conducted on an intention-to-treat principle using all randomized participants. Missing data will be replaced by the last score carried forward. Demographic characteristics and baseline data will be summarised by descriptive statistics. An index will be computed to assess the success of blinding [47]. This index takes the value one for complete blinding and zero for complete lack of blinding.

For outcomes measured using an essentially continuous scale, differences in mean change from baseline to each time point will be compared between groups using linear regression modelling adjusting for baseline levels of the outcome measure. Model assumptions will be checked by standard diagnostic plots [48]. For analysis across all time points simultaneously, accounting for repeated measurements, we will estimate the differences between groups using generalised estimating equation models for the post-baseline measurements with adjustment for baseline measurements, a robust variance and unstructured working correlation [49]. Constancy of the difference between groups over time will be assessed by fitting models which include a term for the interaction between treatment and time. Sensitivity analyses include repetition of analyses with calculation of bootstrap standard errors, and identification of influential individuals by sequentially omitting each participant and refitting the model.

Participant measures of perceived improvement following physiotherapy or placebo treatments will be compared by calculating the relative risks and their 95% confidence intervals at each time point using log binomial regression [50]. Repeated measures relative risk calculations will be performed using generalised estimating equations with a logarithmic link function, robust variance and unstructured correlation [49]. As above, models including a term for the interaction between treatment and time will be fit to assess the constancy of the difference between groups over time.

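### Three unranked primary outcomes, two visits and a pooled model, with no deciding comparison named and a sample size justified for SPADI alone

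*Protocol article*

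**What the plan says.** **Outcomes.** The Abstract states: "The primary outcome measures are self reported questionnaires including the shoulder pain and disability index (SPADI), average pain on an 11-point numeric rating scale", and goes on to the participant's global rating of change. Table 3 (Outcome assessment) lists the same three under its primary heading, the third being "Participant perceived global rating of change overall". The article gives no order among them.

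**Visits.** "Blinded assessment will be conducted at baseline and at 10 weeks and 22 weeks after randomisation". Neither post-baseline visit is called primary.

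**Analyses.** For continuous outcomes, Data analysis says that "differences in mean change from baseline to each time point will be compared between groups using linear regression modelling". It then adds: "For analysis across all time points simultaneously, accounting for repeated measurements, we will estimate the differences between groups using generalised estimating equation models". The global rating is handled in parallel, with relative risks and 95% confidence intervals at each visit and then a repeated-measures version. No lead comparison and no rule for combining outcomes is given.

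**Sample size.** The calculation is "to detect a difference in 10 week SPADI of 10 units", with 91 per group for 80% power at a two-sided 5% level. The same section claims 85% power for SPADI when both visits enter a repeated-measures analysis. Average pain and the global rating have no power statement.

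**After week 10.** The physiotherapy group is asked to continue daily home exercises (Home exercises section). For the other arm: "The placebo participants will not receive any intervention or complete any home exercises during the 12 week follow-up period".

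**The concern.** Three outcomes, each compared at two visits and once across visits, make nine between-group comparisons under the primary label. The article does not say which of them answers the trial's question. A reader of the results could take any one favourable comparison as a positive primary finding, and the plan gives no ground for objecting. The 5% level in the sample size section belongs to a SPADI calculation and does not protect a choice among nine.

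The open choice of visit also matters in substance. The stated aim concerns a 10-week programme. Week 10 compares the programme with placebo. Week 22 compares the programme plus continued home exercise with placebo followed by nothing. Leaving the deciding visit open therefore leaves open which question the trial answers.

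**Working it through.** **1. The plan's own figures.** Inputs from Sample size: difference 10, SD 27, baseline-to-week-10 correlation 0.45, two-sided 5%, 80% power.

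- Baseline-adjusted SD: 27 × √(1 − 0.45²) = 27 × √0.7975 = 24.11.
- n per group = 2 × [24.11 × (1.960 + 0.842) / 10]² = 91.26. The stated 91 gives 79.9% power, so it reproduces.
- Both visits, with correlation 0.8 between post-baseline measurements: SD of the adjusted two-visit mean = 27 × √[(1 + 0.8)/2 − 0.45²] = 27 × √0.6975 = 22.55. Power at 91 per group = 84.9%, so the stated 85% reproduces.

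Both figures are sound, and both are for SPADI.

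**2. Number of comparisons.** 3 outcomes × (week 10, week 22, pooled) = 9. Treatment-by-time interaction tests are not counted.

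**3. Bounds if the tests were independent.** 1 − 0.95³ = 14.3%; 1 − 0.95⁶ = 26.5%; 1 − 0.95⁹ = 37.0%. The tests are correlated, so the nine-test bound is too high.

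**4. Allowing for correlation.** Under no effect, the six outcome-by-visit test statistics were simulated as multivariate normal (400,000 draws). The pooled test for each outcome was taken as the standardised mean of its two visits. Each test was two-sided at 5%.

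- Visit correlation: 0.8 from Sample size, or its baseline-adjusted value (0.8 − 0.2025)/(1 − 0.2025) = 0.75. The protocol gives this for SPADI; using it for the other two outcomes is an assumption.
- Between-outcome correlation: not in the document, so varied from 0 to 0.9.

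Chance of at least one significant result:

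| Between-outcome correlation | 9 comparisons, visit corr. 0.75 | 9 comparisons, visit corr. 0.8 | 3 outcomes, week 10 only |
|---|---|---|---|
| 0 | 22.9% | 22.2% | about 14% |
| 0.5 | 20.1% | 19.2% | about 12.5% |
| 0.7 | 17.5% | 16.9% | about 11% |
| 0.8 | 15.7% | 15.1% | about 10% |
| 0.9 | 13.5% | 13.0% | about 8% |

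SPADI alone, at two visits plus pooled, gives about 8%. An assumed visit correlation of 0.5, weaker than the protocol's, gives 16–26% for the nine comparisons.

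**5. Effect of adjusting instead of ranking.** Bonferroni over the three outcomes (5%/3 = 1.67% each) would need 122 per group for SPADI. At 91 per group it leaves about 66% power.

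**The case against.** **The sample size does not cover SPADI at week 10 alone.** A reader might infer that it does. The 91 per group rests on that comparison, but the section also gives a repeated-measures power over both visits, and that figure is correct. The supportable statement is that only SPADI is powered.

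**No decision rule is stated.** A reader might infer that all nine comparisons are tests at 5% and that any one wins. The document does not say so. The 5% level appears only in the SPADI calculation, Data analysis speaks largely of estimating differences, and nowhere is one significant result declared sufficient. This objection stands: the error rate is conditional on how the results are read.

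**A single unconditional inflation figure is not available.** Values around 25% need nearly uncorrelated outcomes and a visit correlation below the protocol's. Uncorrelated outcomes are implausible here, because one of the two SPADI subscales is pain and average pain is another primary outcome. The lower part of the range deserves more weight than the top.

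**Loss of power if all three outcomes were required.** Requiring all three could not give more power than SPADI alone. But the 80% is claimed for SPADI only, no such requirement is stated, and the document gives no inputs for a joint figure.

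**Week 22 is openly described.** The different regimens after week 10 are disclosed and are not an error. One may also object to placing different questions in one error family. The week-10 figure of 8–14% does not depend on doing so.

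**Multiplicity rules often sit in the analysis plan.** That is fair for the details of adjustment. The choice of primary outcome and visit belongs in the protocol, and here the protocol makes a positive choice of three equal primaries. An equal split of the 5% added later would undercut the stated power (step 5 of the working); an order with SPADI first would not.

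**Conclusion.** The concern holds in this form: three unranked primary outcomes, each compared at two visits and in a pooled model, have no named deciding comparison, and the sample size is justified for SPADI only. The error inflation of 13–23% over nine comparisons, or 8–14% at week 10 alone, holds only if each comparison is read at a nominal two-sided 5% and any one may be presented as a positive primary result. It also rests on the protocol's SPADI visit correlation applying to all three outcomes, and on between-outcome correlations that the document does not supply. Even at a between-outcome correlation of 0.9, the nine-comparison rate is more than twice 5%. This is a design choice that should be tightened; the sample size arithmetic is not at fault.

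**What to change.** Name SPADI at week 10, adjusted for baseline and tested at two-sided 5%, as the single deciding comparison. It is the one from which the 91 per group was derived, so the stated 80% power is kept.

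Test average pain at week 10 and then the proportion *much better* on the overall rating at week 10, in that fixed order, each at 5% and only if the preceding test is significant. This holds the error rate of the week-10 set at 5% without a larger sample.

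Report all week-22 and pooled repeated-measures results as secondary. Describe week 22 as the programme with continued home exercise against placebo with no further treatment.

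The cost is in wording and status. No outcome is dropped from collection or reporting, but two outcomes lose equal primary standing, and the 85% repeated-measures power becomes a property of a secondary analysis.

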**Discussion:**

Results from this trial will contribute to the evidence regarding the effectiveness of a physiotherapy program for the management of CRCP.

**Trial registration:**

NIH Clinical Trials Registry # NCT00415441

## Background

Shoulder disorders are a common cause of musculoskeletal morbidity in the community [1,2], affecting 15–30% of adults at any one time [3] and having their peak prevalence in the mid-to-older age groups [4]. Since moving the shoulder allows placement of the hand, compromised shoulder function impacts substantially on tasks essential to daily living such as dressing, eating, personal hygiene and work [5]. Shoulder pain often impairs the ability to sleep, thus affecting mood and concentration. Hence shoulder disorders can lead to considerable disability, reductions in health-related quality of life, absenteeism from work and substantial utilization of health care resources [5-7].

Shoulder disorders are a common reason for seeking medical care – in Australia, they account for 1.2% of all general practice encounters, being third only to back (3.8%) and neck complaints as musculoskeletal reasons for primary care consultations [8]. They also account for up to 10% of all referrals to physiotherapists [9]. Shoulder disorders are often recalcitrant with persisting pain and disability from 12 [10] to 18 months [11] in up to 50% of cases. Chronic shoulder conditions may require surgical intervention in 15–28% of individuals [12]. Thus, they are a relevant health problem for clinicians, funding providers and health-care policy makers.

Although there is controversy as to exact definitions for different shoulder diagnostic categories, a large proportion of shoulder problems can be classified under the term 'chronic rotator cuff pathology' (CRCP). The term (or its variants such as impingement syndrome) includes a spectrum of pathologies (tears, inflammation, tendonitis, degeneration) involving contractile and other local structures around the shoulder joint [13,14] giving rise to similar signs and symptoms. Pain is the main feature, particularly on overhead movement, at night, and when lying on the affected side. Examination may reveal a painful arc during shoulder elevation, pain on resisted shoulder abduction, external rotation or internal rotation, and a positive impingement test (ref). Restricted shoulder range may be present but is mostly related to pain rather than stiffness per se [15]. Unlike other shoulder conditions, such as adhesive capsulitis, global shoulder passive restriction is not a feature. Diagnosis is traditionally based on history and clinical findings. Investigative procedures such as x-ray, ultrasound or magnetic resonance imaging may be used to demonstrate CRCP or to exclude other less common shoulder pathologies.

It is thought that shoulder impingement is involved in the initiation and/or perpetuation of CRCP. This occurs when the greater tuberosity impinges against the coracoacromial arch in shoulder elevation causing mechanical irritation of local structures [15]. While there is speculation as to whether the pathology seen with CRCP is primary or secondary to impingement, a number of factors can play a role in CRCP [15,16]. In particular, if the rotator cuff muscles do not function in a co-ordinated manner with each other as well as with the principal muscles that move the humerus and scapula, then inadequate stabilisation of the humeral head may occur during shoulder elevation [17,18]. Poor shoulder, cervical and thoracic posture as well as tight structures can also contribute to dysfunctional movement patterns [19,20] and ultimately chronic pathology and pain.

Physiotherapy is often the first line of management for CRCP [21]. In a survey of approximately 800 primary care medical practitioners, 79% stated that their usual treatment of a patient with CRCP would be referral to a physiotherapist [21]. Physiotherapy aims to reduce pain and disability by improving the biomechanics and movement patterns of the shoulder complex rather than by treating the pathology *per se*. In clinical practice, patients with CRCP receive a combination of physiotherapy interventions in order to effectively address the modifiable factors contributing to pain and dysfunction.

While physiotherapy is commonly prescribed for CRCP, at present there is little conclusive evidence to support or refute its effectiveness, and no formal evaluation of its cost-effectiveness. In a Cochrane review, 11 trials were identified that evaluated physiotherapy for CRCP [22]. No firm conclusions were able to be drawn given the variable methodological quality of the trials and the fact that many tested a single physiotherapy modality with few testing combined modalities despite this being the most common way in which shoulder disorders are treated in practice. Furthermore, eight of the 11 (72%) CRCP trials evaluated electrotherapy modalities which are generally not recommended by expert clinicians as the most appropriate physiotherapy modality to treat CRCP. From the trials in CRCP or in mixed shoulder disorders that were included in the review, there was some evidence to propose that exercise may be effective, with additional benefit from mobilisation [23-26]. Recent trials identified since this Cochrane review still fail to clarify the effectiveness of physiotherapy for CRCP given differences in the treatment program, comparison group and outcomes [27-30]. The need for further clinical trials in this area is supported by the conclusions and recommendations of other recent systematic reviews [31-33].

Therefore, the aim of this trial is to determine whether a 10-week multimodal physiotherapy program reflective of current physiotherapy practice improves pain, disability and health-related quality of life and is more cost-effective than placebo in individuals with CRCP.

## Methods/Design

### Design

This will be a randomised placebo controlled trial with blinded participants and outcome assessors (Figure 1). The trial comprises a 10-week intervention and a 12-week follow-up (Figure 1). Participants will be assessed immediately before treatment (baseline), immediately after treatment (final) and at 22 weeks (follow-up) post randomisation. The assessments will be performed by the same assessor who will be blind to group allocation.

**Figure 1 F1:**
[figure not shown]
Trial profile.

### Participants

A community sample will be recruited in Melbourne, Australia through orthopaedic and rheumatology outpatient clinics, community-based practices and general practitioners as well as by advertising in print and radio media. Inclusion criteria will be: (i) aged over 18 years; (ii) shoulder pain for greater than 3 months; (iii) pain severity on movement rated at least 4/10 on an 11 point numeric rating scale; (iv) pain on active abduction or external rotation and; (v) positive shoulder impingement quick test [34]. Exclusion criteria will be: (i) resting shoulder pain of greater than 7/10 in severity; (ii) reason to suspect a complete rotator cuff tear eg. substantial shoulder weakness, a positive drop-arm sign or a high riding humerus observed on plain xray; (iii) prior shoulder surgery; (iv) radiological evidence of shoulder osteoarthritis, shoulder joint calcification or prior fracture; (v) systemic pathology including inflammatory joint disease or neoplastic disorders; (vi) more than 50% restriction of passive range of motion in two or more planes; (vii) shoulder pain referred from vertebral structures diagnosed via spinal clearing tests [35]; (viii) symptoms of complex regional pain syndrome; (iix) active intervention in last 3 months including corticosteroid/hydrodilatation injection or physiotherapy; (ix) anti-inflammatory medication in past two weeks; (x) inability to understand written and spoken English.

A diagnosis of CRCP by a medical doctor supported by a plain x-ray of the shoulder will be necessary for potential inclusion. All volunteers will then be required to undergo a physical examination with a physiotherapist to screen for signs and symptoms, and to exclude shoulder pain that is not due to rotator cuff origin (eg, neural or cervical referral, adhesive capsulitis). Participants with bilateral CRCP symptoms will be asked to indicate which shoulder is the most symptomatic. This shoulder will be treated. Those with equally symptomatic shoulders will receive treatment for the shoulder of the dominant limb.

The Royal Melbourne Hospital Human Research Ethics Committee approved the study (Project #2001.115) and all participants will provide written informed consent.

